## Methods and analysis

### Study design

The design of this study is a randomized controlled trial, strictly following the Standard Protocol Items: Recommendations for Interventional Trials (SPIRIT) statement (see Additional file 1) [25]. The allocation will be hidden, and the allocation ratio will be 1:1:1. A total of 360 eligible participants will be randomly assigned to the TiaoshenYizhi acupuncture group, the sham acupuncture group, and the control group. Participants will be evaluated at baseline (weeks -2 to 0) and weeks four, eight, and 12. EEG will be used to explore the diagnostic value of event-related potential (ERP) in aMCI, and fMRI will be used to measure the structure and function of brain regions related to episodic memory at baseline and eight weeks. All data collectors will not know the group assignment. The research procedure and results evaluation schedule of this trial are shown in Fig. 1 and Table 1.

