### Sample size

MoCA score of the cognitive function assessment scale will be used as an effect index to evaluate the recovery of cognitive function in patients with MCI. According to the previous study and clinical experience, it has been estimated that the MoCA score difference between the elderly with MCI and the baseline after eight weeks of acupuncture was 5.50 ± 2.48 points, and the MoCA score difference of the control group was 4.88 ± 2.45 points [37]. On this basis, the calculated effect quantity is 0.17, and by the two-sided test, α = 0.05, β = 0.20, calculated by gpower 3.1.9.2 software, and the sample size is 300 cases. Considering the loss of follow-up rate of 20%, the total sample size of this study is 360 cases, i.e., 120 cases in each group.

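### The 20% loss allowance is added to 300 rather than taken from the number randomised, so 360 leaves 288 observed outcomes, not the 300 required

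*Protocol article*

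**What the plan says.** The Sample size section of the protocol article takes three steps.

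- **Requirement.** With "by the two-sided test, α = 0.05, β = 0.20" and an effect size reported as "the calculated effect quantity is 0.17", the total was "calculated by gpower 3.1.9.2 software, and the sample size is 300 cases".
- **Loss.** A 20% loss to follow-up is assumed: "Considering the loss of follow-up rate of 20%, the total sample size of this study is 360 cases".
- **Total.** The result is "the total sample size of this study is 360 cases, i.e., 120 cases in each group".

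The Study design section repeats the total of 360 and says "the allocation ratio will be 1:1:1", so the 300 corresponds to 100 per arm. The article gives no other loss rate and no other basis for 360. Its Statistical analysis section plans multiple imputation for missing data.

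**The concern.** A loss to follow-up rate is a proportion of the participants who enter the trial. To finish with a required number, that number must be divided by one minus the loss rate. Here the total appears to have been reached by adding 20% of the requirement, which always falls short of the stated loss.

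If so, the trial would miss its own target at exactly the loss it plans for, and the stated 80% power would not hold at that loss. The Discussion section names keeping participants in treatment and in outcome collection until the end as the main challenge of the study, so the allowance covers a risk that the authors themselves regard as real.

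**Working it through.** **Inputs, all from the Sample size section unless noted**

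- Requirement before loss: 300 in total. At 1:1:1 (Study design section) this is 100 per arm.
- Loss to follow-up, d: 0.20.
- Total to be randomised: 360, or 120 per arm.
- Two-sided α 0.05, power 0.80.
- Effect size 0.17, type not named.

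**Step 1. Reproduce the plan's total**

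n × (1 + d) = 300 × 1.20 = 360. Per arm, 100 × 1.20 = 120. Both match the plan exactly, so this is how 360 arises.

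**Step 2. What 360 leaves at the planned loss**

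360 × (1 − 0.20) = 288. Per arm, 120 × 0.80 = 96. The shortfall is 300 − 288 = 12 in total, 4 per arm, or 12 / 300 = 4%.

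**Step 3. The loss that 360 does cover**

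1 − 300 / 360 = 60 / 360 = 16.7%.

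**Step 4. The total that keeps 300 at 20% loss**

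n / (1 − d) = 300 / 0.80 = 375, or 125 per arm. Check: 375 × 0.80 = 300. The plan is 375 − 360 = 15 below this.

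**Step 5. Effect on power**

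The article does not name the test or the type of effect size. This step assumes a one-way ANOVA with three groups and reads 0.17 as Cohen's f. Power is the upper tail of a noncentral F with 2 and N − 3 degrees of freedom and noncentrality λ = N × f².

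| Observed N | λ = N × 0.17² | Power |
|---|---|---|
| 300 | 300 × 0.0289 = 8.67 | 75.0% |
| 288 | 288 × 0.0289 = 8.32 | 73.1% |

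The loss step costs 75.0 − 73.1 = 1.9 points.

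Alternatively, accept that 300 gives 80% in such a test, which corresponds to f of about 0.18. Power at 288 is then about 78.2%, a cost of about 1.8 points. The size of the loss is therefore almost the same under either reading.

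**The case against.** The strongest objection is that this is too small to matter. Twelve outcomes and about 2 points of power change no arm, endpoint or analysis. The 20% is itself a round planning figure, and an actual loss of 16.7% or less would leave 300. The point about size stands and sets the weight of the finding. It does not make the three printed figures agree.

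A second objection is that multiple imputation keeps all 360 in the analysis, and that participants lost before week 8 may still contribute baseline and week-4 MoCA scores. The information lost may therefore be somewhat less than 20%. That is fair, and it is why the count here is of participants with an observed outcome. But imputation does not restore outcomes that were never measured, and the plan itself inflates for loss, so it already treats lost outcomes as a cost.

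A third objection is that the power figures depend on an assumption. The article does not say that 0.17 is Cohen's f. The Abstract names repeated-measures ANOVA and a mixed linear model, while the Statistical analysis section names one-way ANOVA. This stands: 75.0% and 73.1% are conditional. The count of 288 against 300 needs no such assumption.

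Finally, setting 73.1% against the planned 80% would overstate this point. Of that gap of 6.9 points, 5.0 arise because 300 does not give 80% power at f = 0.17 in a one-way ANOVA (339 would be needed). Only 1.9 belong to the loss step.

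**Conclusion.** The concern holds. On the article's own figures, 360 randomised with 20% loss leaves 288 observed outcomes (96 per arm), 12 short of the stated requirement. Keeping 300 takes 375. This part is plain arithmetic and rests only on reading the 20% as the proportion of randomised participants lost, which is what a loss to follow-up rate means.

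The consequence is minor: about 2 points of power, under the three-group one-way ANOVA assumption used above. It is a slip that should be corrected, not a threat to the design.

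The finding covers the loss step only. Whether 300 is the right starting figure is a separate and larger question, and correcting the inflation does not answer it.

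**What to change.** Replace the closing sentence of the Sample size section with one of the following.

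- **Keep 360.** State that 360 randomised (120 per arm) gives 288 participants with an observed outcome (96 per arm) at 20% loss, or 300 if loss is at most 16.7%. Quote the power for 96 per arm, naming the test and the type of effect size. This costs one corrected sentence plus the power figure, and no extra participants.
- **Keep 300 at 20% loss.** Raise the total to 375 (125 per arm), 15 more than planned, and change the 360 in the Abstract and the Study design section to match. The Trial status section reports 37 recruited by 12 August 2022, so at that date either course was still open.

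Make the change together with any re-derivation of the 300. If that figure moves, the new requirement should be divided by 0.80, and both 360 and 375 are superseded.

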### Statistical analysis

Statistical analysis will be performed using SPSS software V.26.0 (IBM) package by an independent statistician, with a statistical significance of *P* value < 0.05 on both sides. Categorical variables will be described as frequencies or percentages using a chi-square test. For the normal distribution, continuous variables will be expressed using mean ± standard deviation (SD) and will be assessed by one-way analysis of variance (ANOVA) and compared between every group. For non-normal distribution, continuous variables will be expressed using the median and its interquartile range (IQR) and be analyzed by the rank sum test. The missing data will be filled in using the multiple imputation method. When baseline index imbalances occur among the three groups, a general linear model or logistic regression model will be applied for the calibration and analysis.

Adverse effects (AEs) will be analyzed using a Chi-square test or Fisher’s exact test. If the formal statistical analyses between groups cannot be performed due to the lack of power, AEs will be tabulated and summarized using descriptive statistics. For fMRI data, DPABI (a toolbox for Data Processing & Analysis for Brain Imaging, Version 2.3_170105, http://rfmri.org/dpabi) software package will be used to preprocess the image data obtained by fMRI scanning under the Matlab2013a (The Match Works, Inc). Independent component analysis (ICA) will be used to extract time signals for sequence dynamic causal modeling (DCM) analysis. Components will be extracted from the preprocessed images using GIFT v4.0 (http://icatb.sourceforge.net/).

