**Methods:**

In this multicenter, parallel-group, double-blind, randomized controlled trial, 360 aMCI participants will be recruited from six subcenters and randomly assigned to the acupuncture group, sham acupuncture group, and control group. The acupuncture group will receive *TiaoshenYizhi* (TSYZ) acupuncture, the sham acupuncture group will use streitberger sham acupuncture, and the control group will only receive free health education. Participants in the two acupuncture groups will receive real acupuncture treatment or placebo acupuncture three times per week, 24 sessions over 8 consecutive weeks. The primary outcome will be global cognitive ability. Secondary outcomes will be a specific cognitive domain, including episodic memory and execution ability, electroencephalogram, and functional magnetic resonance imaging data. Outcomes will be measured at baseline and the fourth and eighth weeks after randomization. Repeated measurement analysis of variance and a mixed linear model will be used to observe the intervention effect.

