### Outcome assessment

The variables in this trial consist of demographics and clinical characteristics, primary outcomes, and secondary outcomes. The basic characteristics will be measured at baseline (1–2 weeks before randomized allocation). Primary and secondary outcomes will be measured at baseline, the middle of intervention (4 weeks), the end of intervention (8 weeks), and 4 weeks of follow-up. Outcomes of fMRI and EEG will be measured at baseline and the end of intervention (8 weeks). All outcomes will be evaluated by experienced doctors who will be blinded to the allocation results of participants. A summary of all measurements in this trial is shown in Table 2.

**Table 2 Tab2:** Trial processes chart

Study period Item	Enrolment and Baseline	Intervention Period (8 weeks, one time per 4 weeks)				Follow-up phase
**Week**	-2 to 0	1 to 3	4	5 to 7	8	12

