The characteristics of acupuncture treatment make it difficult to implement the double-blind method; therefore, we will blind participants by setting up the sham acupuncture group as a placebo [28, 50]. Considering the placebo effect of sham acupuncture, the health education group will be set up as a negative control group, providing prevention knowledge of common geriatric diseases, including AD. We increased the sample size and expanded the scope of the crowd compared with our previous research. The intervention can be implemented in community medical centers, and the adverse events can be fully evaluated. The main challenge of this study is whether such a large number of patients with aMCI are willing to receive acupuncture treatment until the end of the study and cooperate with the collection of each outcome. We will give material rewards to the participants.

In conclusion, through this study, the effectiveness of TiaoshenYizhi acupuncture on the episodic memory of patients with aMCI will be further clarified. We expect that this study will provide a reference for early treatment of aMCI and AD. The results of the study will be reported according to the guidance of the Consolidated Standards of Reporting Trials statement (STRICTA) [51].

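### All three pairs of arms are compared at two-sided 0.05 over three post-baseline visits, and no primary contrast or visit is declared for MoCA

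*Protocol article*

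**What the plan says.** - **Comparisons.** Statistical analysis sets significance at two-sided 0.05 and says that normally distributed continuous variables "will be assessed by one-way analysis of variance (ANOVA) and compared between every group". Non-normal variables get a rank sum test. The section does not say whether the pairwise tests depend on the ANOVA, and it does not mention visits.
- **Arms.** Study design has three arms, and "the allocation ratio will be 1:1:1".
- **Visits.** Outcome assessment gives "the middle of intervention (4 weeks), the end of intervention (8 weeks), and 4 weeks of follow-up" as the post-baseline measurements, so weeks 4, 8 and 12. The Abstract differs: "Outcomes will be measured at baseline and the fourth and eighth weeks after randomization".
- **Model.** Only the Abstract says how the treatment effect is analysed: "Repeated measurement analysis of variance and a mixed linear model will be used to observe the intervention effect". Statistical analysis names neither method.
- **Implied contrast.** Sample size uses the eight-week MoCA change under acupuncture (5.50, SD 2.48) against a control group (4.88, SD 2.45), "by the two-sided test, α = 0.05, β = 0.20". It does not say whether that control stands for sham or for health education.
- **Role of the arms.** The Discussion presents sham as the placebo. Because sham may itself have a placebo effect, "the health education group will be set up as a negative control group".

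**The concern.** Three arms give three pairs, and the primary outcome has up to three post-baseline visits. With no declared pair or visit, a significant result in any of up to nine comparisons could be presented as the trial's positive finding. The reader could not say what its error rate was.

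The pairs also answer different questions. TSYZ versus sham addresses a specific needle effect. Either needle arm versus education compares 24 treatment sessions in eight weeks with education once every four weeks, about 8/4 = 2 sessions, so it also carries attention and expectation. A three-arm test does not separate these questions.

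**Working it through.** **Is there a stated figure to reproduce?** The article gives no familywise error rate. Its sample size does not identify the decisive test either. A one-way ANOVA with three groups and f = 0.17 needs 337 in total (339 in equal arms) for 80% power, and 300 gives 75%. A repeated-measures between-group test with an unstated correlation near 0.8 comes close (306 with two measurements, 294 with three). That mismatch is a separate matter; here it means only that the primary test cannot be inferred from the 300.

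**Inputs.** Three equal arms; three pairs; two-sided 0.05; visits at weeks 4, 8 and 12 (or weeks 4 and 8 from the Abstract). The correlation of MoCA between visits is not given, so a common value ρ from 0.3 to 0.9 is assumed.

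**One visit, no gate.** The chance that at least one of three pairwise tests rejects under the global null is the upper tail of the studentized range for three groups at 1.96 × √2 = 2.77. That is 0.122.

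**One visit, ANOVA gate.** If pairs are examined only after a significant three-arm ANOVA, a false claim under the global null first needs a false rejection by the ANOVA: 5.0%. If one arm truly differs, only one true null pair is left, tested at 5%. With exactly three arms the gate is therefore enough.

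**Three visits.** Simulation under the global null, 200,000 runs per setting, any pair at any visit:

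| ρ (assumed) | ungated | gated at each visit |
|---|---|---|
| 0.3 | 31.0% | 13.7% |
| 0.5 | 28.5% | 12.7% |
| 0.7 | 25.0% | 11.2% |
| 0.8 | 22.5% | 9.9% |
| 0.9 | 19.5% | 8.5% |

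As a check on the gated column, three independent visits would give 1 − 0.95³ = 14.3%; the simulation at ρ = 0 gives 14.2%. With the Abstract's two visits, ungated error is 22.4% to 16.7% and gated error 9.6% to 7.1% for ρ from 0.3 to 0.9.

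**What an overall test can show.** Suppose, as an illustration, that both needle arms reach 5.50 and education 4.88, so there is no specific needle effect.
- Pooled SD = √((2.48² + 2.45²)/2) = 2.465.
- Grand mean = (5.50 + 5.50 + 4.88)/3 = 5.293; deviations are 0.207, 0.207 and −0.413.
- f = √((0.207² + 0.207² + 0.413²)/3)/2.465 = 0.292/2.465 = 0.119.
- With 300 analysed, the three-arm ANOVA is significant with probability 43%.

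**Power of one pairwise test at the article's own difference.** d = (5.50 − 4.88)/2.465 = 0.2515. With 100 per arm, 0.2515 × √(100/2) = 1.778, and Φ(1.778 − 1.960) = 0.428. The same formula gives 41% with 96 per arm and 50% with 120. For 80% power, 2 × (1.960 + 0.842)²/0.2515² gives 249 per arm.

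**The case against.** A reader might infer that the plan carries a flat false-claim rate of 12-28%. The article does not support that. Those figures need pairwise tests that ignore the ANOVA named in the same sentence. The upper one also needs separate testing at three visits and a correlation near 0.5, and the article states none of these. An ANOVA followed by comparison of the groups reads at least as naturally as a gated procedure, which holds 5% at one visit. The Abstract's repeated-measures or mixed model could supply a single test. A post-hoc adjustment may sit in a statistical analysis plan that is not shown, so its absence here is no fault.

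It is also fair that a contrast and visit are implied: MoCA is the only primary outcome, the sample size looks at eight weeks, and the Discussion gives sham and education their roles.

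This limits the size of the point but does not remove it. Reaching 5% takes a gate and one decisive visit, or one decisive model test, and none is declared. The implied contrast is unclear: elsewhere in the article the control group is the education arm, while the placebo rationale points to sham. The Abstract and the body disagree on both model and visits. And neither a gate nor a group-by-time test shows that a positive result comes from TSYZ versus sham.

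**Conclusion.** The point holds as a failure to fix the confirmatory test. The article states a rule for all pairs at 0.05, leaves the deciding contrast and visit undeclared, and gives versions of the analysis and visit schedule that do not match. The error rate cannot be stated as one number. It is about 5% (gated) or 12% (ungated) at one visit, and about 8.5-14% (gated) or 19.5-31% (ungated) at three. The three-visit figures rest on the assumed correlation of 0.3-0.9, equal arms and the global null. The interpretive gap does not depend on those assumptions: on every reading, an overall positive result may reflect only a contrast with education.

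**What to change.** Declare one primary test: TSYZ versus sham, MoCA at week 8, two-sided 0.05, estimated from the mixed linear model that the Abstract names. This follows the Discussion's placebo rationale and the time point in Sample size. If it is significant, test TSYZ versus health education at week 8 at 0.05, in fixed sequence. Report sham versus education, and weeks 4 and 12, as supportive, with confidence intervals and no confirmatory claim. Reconcile Statistical analysis with the Abstract on the model, and the Abstract with Outcome assessment on the week 12 visit. State which arm the control group in Sample size stands for.

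If the sponsor prefers to keep all three pairs, testing them at week 8 only after a significant ANOVA holds 5%. Bonferroni at 0.0167 gives 4.4%, but cuts pairwise power at the article's difference to 27% with 100 per arm. Neither makes TSYZ versus sham decisive.

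The text change is a paragraph by dated amendment before outcomes are analysed, and the fixed sequence splits no alpha. There are two real costs. TSYZ versus education cannot be claimed if the first test fails. And if the article's 0.62-point difference applies to sham, that first test has only about 43% power with 100 per arm, so the stated 80% should be restated for this contrast.

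### The abstract and the Statistical analysis section name different efficacy analyses, and the section adjusts for baseline only if imbalance is observed, which costs power

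*Protocol article*

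**What the plan says.** The abstract (Methods) states: "Repeated measurement analysis of variance and a mixed linear model will be used to observe the intervention effect".

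The Statistical analysis section names neither method. It has three elements:
- One-way ANOVA across the groups for normally distributed continuous variables.
- For non-normal variables, a median and interquartile range, to "be analyzed by the rank sum test".
- Adjustment on a condition: "When baseline index imbalances occur among the three groups, a general linear model or logistic regression model will be applied". No criterion for imbalance and no covariates are given.

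Missing data are to be multiply imputed. The section does not say whether the ANOVA is run on scores or on changes from baseline.

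Two other parts of the protocol matter here. The Outcome assessment section and Table 2 schedule MoCA, the primary outcome, at baseline and at weeks 4, 8 and 12. The Sample size section is built on MoCA change over eight weeks: a change that "after eight weeks of acupuncture was 5.50 ± 2.48 points" in one group, and "the MoCA score difference of the control group was 4.88 ± 2.45 points".

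**The concern.** The two places describe different efficacy analyses. Condensing a protocol into an article explains missing detail, but not two different answers to the same question. Any separate analysis plan would have to depart from one of them.

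The rule in the Statistical analysis section is also poor in itself. In a randomised trial, baseline differences between arms arise by chance. The reason to adjust for baseline MoCA is that it predicts later MoCA, and this is equally true when the arms look balanced. A rule that waits for visible imbalance leaves the default, unadjusted test in place in nearly every trial.

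At stake are power and a primary test that can be identified before the data are seen. The ANOVA and rank sum branches also do not estimate the same quantity.

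**Working it through.** **1. The plan's own figure.** The Sample size section takes an effect size of 0.17 and reports its result as follows: "by the two-sided test, α = 0.05, β = 0.20, calculated by gpower 3.1.9.2 software, and the sample size is 300 cases". Read as Cohen's f for a three-group one-way ANOVA (an assumption, since the type is not named), the noncentrality is λ = N f² = 300 × 0.17² = 8.67. Power is then 75.0%, and 80% needs N = 339. So 300 is not reproduced on this reading. That is a separate sample-size matter, and nothing below depends on it.

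**2. Inputs for the comparison.**
- From the protocol: 120 per arm less 20% loss gives 120 × 0.8 = 96 per arm (288 in total); two-sided α = 0.05.
- Assumed: an effect of 0.3 SD of the week-8 score in one arm; equal SDs at baseline and week 8; correlation r between baseline and week-8 MoCA of 0.3 to 0.7; imbalance declared when a baseline one-way ANOVA has p < 0.05.

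**3. Formulas.** With one arm shifted by 0.3, λ for week-8 scores is 96 × (2/3) × 0.3² = 5.76. The residual variance is 1 for scores, 2(1 − r) for change and 1 − r² for ANCOVA. Dividing 5.76 by each gives λ, and the noncentral F with 2 numerator degrees of freedom gives power. Power under the conditional rule was simulated (40,000 trials per setting).

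| r | λ score / change / ANCOVA | Score ANOVA | Rule, scores | Change ANOVA | Rule, change | Always ANCOVA |
|---|---|---|---|---|---|---|
| 0.3 | 5.76 / 4.11 / 6.33 | 56% | 56% | 42% | 42% | 60% |
| 0.5 | 5.76 / 5.76 / 7.68 | 56% | 56% | 56% | 56% | 69% |
| 0.6 | 5.76 / 7.20 / 9.00 | 56% | 57% | 66% | 67% | 77% |
| 0.7 | 5.76 / 9.60 / 11.29 | 56% | 57% | 79% | 80% | 86% |

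Repeat simulations differ by about one percentage point. Under randomisation the trigger fires in only about 5% of trials, so the rule almost equals its default test.

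**4. The same check with the plan's f = 0.17 and N = 300** (r = 0.3 / 0.5 / 0.7):
- If 0.17 is on the week-8 score scale, the rule on scores gives 75 / 76 / 76% and constant adjustment 79 / 87 / 97%.
- If 0.17 is on the change scale, the rule on changes gives about 76% throughout and constant adjustment 91 / 87 / 82%.

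**5. Type I error of the rule under the null.** Across simulations it is about 3.5-4.9%, on scores or on changes. The rule is conservative.

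The normality switch was not simulated, because the protocol gives no criterion for it.

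**The case against.** **The section may be generic.** Its sentences on normal and non-normal variables also cover description and may be meant for all variables, with the abstract's models intended for the longitudinal effect. Those models would use baseline MoCA. This is a fair reading, and it makes the power loss conditional on the Statistical analysis section governing. It does not remove the conflict, because the section that should state the efficacy analysis omits the models, and the imbalance trigger stands in the text on either reading.

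**The ANOVA may be on change scores.** The sample-size inputs are changes, so this is at least as natural as raw scores. A reader might infer that the plan throws away nearly all the information in baseline MoCA. That does not hold at higher correlations: at r = 0.7 change scores reach 79%, against 86% for ANCOVA. The gain from constant adjustment remains, but it is smaller there. At r = 0.3 the gain over raw scores is also small (56% to 60%).

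**Type I error.** A reader might infer that a data-dependent rule inflates false positives. Followed mechanically, it does not. A rate of about 9.5-10.3% arises only if the analyst may choose freely among score ANOVA, change ANOVA and ANCOVA after seeing the results, and the protocol describes no such choice.

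**Detail left to an analysis plan.** Covariance structure, baseline-by-visit terms and models for the secondary outcomes belong there. Silence on centre is not an error in itself, and the planned multiple imputation is not at fault.

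**Conclusion.** The point holds as a contradiction between the abstract and the Statistical analysis section, together with a badly chosen adjustment rule. If the section is followed, power in the illustrated setting is 56-57% on week-8 scores, or about 42 to 80% on change scores, against about 60 to 86% with baseline MoCA always in the model. In every setting run, constant adjustment was the most powerful of the analyses compared.

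The size rests on an assumed correlation of 0.3-0.7, an assumed 0.3 SD effect, and an assumed p < 0.05 trigger. With no correlation there would be no gain over score ANOVA. The harm is lost power and an unfixed primary test, not an inflated false-positive rate. The effect of the normality switch is not quantified.

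**What to change.** Name one primary analysis, in the same terms in the abstract and the Statistical analysis section. The mixed linear model that the abstract already names would serve, or ANCOVA, for MoCA with the week-8 group difference as the result. Adjust for baseline MoCA always, and for centre (the abstract says "360 aMCI participants will be recruited from six subcenters"), whatever balance is observed. Delete the imbalance trigger. Keep the rank test as a sensitivity analysis only, so that distribution no longer selects the primary test. Multiple imputation may stay as planned.

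The cost is a change of wording. Baseline MoCA and centre are known for every participant, no visit or measurement is added, and the sample size is unaffected. The article reports 37 of the planned 360 recruited at its stated date.
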